## Abstract

**Background:**

Alcohol-related violence in and in the vicinity of licensed premises continues to place a considerable burden on the United Kingdom’s (UK) health services. Robust interventions targeted at licensed premises are therefore required to reduce the costs of alcohol-related harm. Previous evaluations of interventions in licensed premises have a number of methodological limitations and none have been conducted in the UK. The aim of the trial was to determine the effectiveness of the Safety Management in Licensed Environments intervention designed to reduce alcohol-related violence in licensed premises, delivered by Environmental Health Officers, under their statutory authority to intervene in cases of violence in the workplace.

**Methods/Design:**

A national randomised controlled trial, with licensed premises as the unit of allocation. Premises were identified from all 22 Local Authorities in Wales. Eligible premises were those with identifiable violent incidents on premises, using police recorded violence data. Premises were allocated to intervention or control by optimally balancing by Environmental Health Officer capacity in each Local Authority, number of violent incidents in the 12 months leading up to the start of the project and opening hours. The primary outcome measure is the difference in frequency of violence between intervention and control premises over a 12 month follow-up period, based on a recurrent event model. The trial incorporates an embedded process evaluation to assess intervention implementation, fidelity, reach and reception, and to interpret outcome effects, as well as investigate its economic impact.

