## Background

Alcohol related violence continues to place a considerable burden on health services [1]. Approximately 70% of unscheduled Accident and Emergency (A&E) attendances are alcohol related at peak times [2], with the bulk stemming from activities in the night time economy (NTE) [3,4]. Urban centres characterised by a high density of premises licensed for the on-site sale and consumption of alcohol typically produce a substantial share of all alcohol-related harm and are associated with severe intoxication and violent injury [5,6]. There is a growing literature detailing environment-specific risk factors in the on-licensed trade [4,7] and recognition that interventions that address these are urgently required [8,9]. However, the number of front-line police staff available to manage this environment is decreasing [10] and in the UK there is growing reliance on unevaluated industry-sponsored schemes. There is therefore a need for robust, formally evaluated interventions that can be routinely adopted by partners involved with managing the NTE. Previous evaluations of premises level (PL) interventions have a number of methodological limitations and none have been conducted in the UK.

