### Recruitment

Licensed premises were identified by searching police incident data and identifying those premises in which violent incidents were detected in the period May 2011 to April 2012. Police data provides the best way of measuring violence in licensed premises as they are routinely available across the study area. Although a proportion of violent incidents are not reported to the police, these data remain the most detailed and accurate records of incidents at the premises level. Other data sources such as Emergency Department attendance data are not universally available. Police incident data are broadly consistent across the 22 LAs taking part in the trial. In order to access police data, data sharing agreements were prepared and signed between Cardiff University and all four police forces in Wales. The agreements cover the period from May 2011 to the end of the trial follow-up period (April 2014). Data containing all violence against the person incidents were encrypted and anonymised before being given to members of the research team for screening. Incidents inside and in the immediate vicinity of licensed premises were identified from the police data based on the inclusion and exclusion criteria listed above. Premises receive the intervention as part of usual practice and as such, premises do not consent to participate in the trial and so withdrawal and loss to follow-up from the intervention phase of the trial is not possible.

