### Randomisation

Premises are stratified by LA, licensable hours (up to 11 pm, open beyond 11 pm), and number of violent incidents in the twelve month period between May 2011 to April 2012 and randomly allocated into control or intervention group. Optimal allocation was used to carry out the randomisation [20], which was carried out by an independent statistician within the South East Wales Trials Unit (SEWTU). The randomised sample of 600 licensed premises comprises the intention to treat (ITT) population.

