### Risk-audit

The intervention is a Risk Led Intervention (RLI) developed from literature documenting features of premises that contribute to harm [21-23]. These interventions involve an initial risk-audit followed by an action plan which is given to the DPS. If the action plan is adopted, risks that promote harm within the premises will have been addressed and a reduction in alcohol-related harm is expected. Action plans require premises to make changes to operating procedures (e.g. reducing capacity, changing how security staff are deployed, checking patrons’ age at the door), improve staff training, as well as covering aspects of the internal and external environment (such as improving surveillance).

The RLI is made up of three components: first, EHOs audit intervention premises to identify areas that might increase the risk of violence, with findings recorded on a risk-audit form (see list of Information recorded by EHO’s on the risk-audit form(s)). For each area of premises operation covered by the risk-audit, EHOs record as much information as possible before giving an RCI score which corresponds with the perceived level of risk. Second, EHOs then record what further action (if any) is required at the premises. If risks are identified EHOs could respond in one or more of the following ways: 1) advise premises to make changes, i.e. verbally or by informal letter; 2) formally require changes to be made, i.e. by serving an improvement notice; 3) refer premises to police and LA licensing officers (who are able to place conditions on premises licenses); 4) a prohibition notice could be served to close the premises without notice if risks present a clear and immediate danger to the public. EHOs will conduct a second audit in premises where further action is required to assess whether the required changes have been made (and enforce where appropriate). The second audit will focus only on areas of risk identified in the initial audit. Depending upon the severity of the risk identified in the initial audit, the second audit will take place either one month (for serious risks) or three months (less serious risks) later, consistent with EHO usual practice. Following the initial risk-audit, EHOs will encourage intervention premises DPS and bar staff to access web-based training and instructional materials designed to engage them in harm reduction practices.

Information recorded by EHOs on the risk-audit form(s)

Audit date*

Audit start and end times*

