As SMILE is additional to the usual practice received by licensed premises from statutory authorities, all costs are incremental. These include 1) EHO training: the time spent by trainers and EHOs on all training related activities will be monitored prospectively, valued using standard methods [27] and amortised over 5 years. The cost of materials, venues and any other resources used in training will also be monitored and valued using money costs incurred. 2) EHO Intervention: The time spent by EHOs in all intervention associated activities relating to each premises, including travel time, will be monitored prospectively and valued using standard methods. 3) Licensee born costs: data of the changes identified in the audits (e.g. installation of CCTV cameras, employment of additional staff, staff training) will be used to estimate the costs of the intervention to licensees. In addition, estimates of the potential cost savings to the health service and criminal justice system resulting from reductions in violent events will be made

#### **
*Effects*
**

The unit of effectiveness for the cost effectiveness analysis will be sessions with one or more violent events, based on police records. An Andersen-Gill model will be applied to account for potential time varying covariates and censoring. The analysis will be carried out using the recurrent event model on the total number of sessions with violent events. The corresponding hazard ratio provides the percentage reduction in risk of a session involving alcohol related violence.

#### **
*Cost-effectiveness analysis*
**

The net cost of the intervention will be assessed against the unit of effectiveness. Uncertainty will be explored through a series of one way and multivariate sensitivity analyses. Results will be reported in the form of an incremental cost effectiveness ratio (ICER) that shows the additional cost per violence-event-session averted and which can be used to demonstrate the relative cost effectiveness of SMILE versus other interventions in future evaluations. A probabilistic sensitivity analysis will be carried out using a non-parametric bootstrap method on the joint distribution of costs and effects [28]. This provides a probability value of an intervention being cost-effective within a range of willingness-to-pay (WTP) threshold values. This helps policy makers to decide whether the intervention is value for money.

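### The premises-level hazard ratio cannot tell prevented violence from displaced violence, yet the societal cost-effectiveness ratio counts the whole modelled reduction as sessions averted

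*Protocol article*

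**What the plan says.** **Allocation.** The abstract gives the design as "A national randomised controlled trial, with licensed premises as the unit of allocation". The Randomisation section adds: "Premises are stratified by LA, licensable hours (up to 11 pm, open beyond 11 pm), and number of violent incidents". Both arms therefore sit inside the same LAs. The article describes no grouping by town centre or street and no buffer between arms.

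**Setting.** The Background says: "Urban centres characterised by a high density of premises licensed for the on-site sale and consumption of alcohol typically produce a substantial share" of alcohol-related harm.

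**Levers.** The Risk-audit section gives as examples of required changes "reducing capacity, changing how security staff are deployed, checking patrons’ age at the door". At the extreme, a prohibition notice can close the premises.

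**Outcome.** The Recruitment section says: "Incidents inside and in the immediate vicinity of licensed premises were identified from the police data". The Main analysis compares the 600 premises as randomised, using an Andersen-Gill model.

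**Economics.** The evaluation takes a societal perspective. Its effects come from the same recurrent event model, its result is the "additional cost per violence-event-session averted", and savings to the health service and criminal justice system are to be estimated from the reduction in violence.

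**Nearest related items.** The secondary outcomes list contamination between arms as a process-evaluation topic. The Main analysis also plans a volume-of-violence analysis limited to study premises, and an observational re-estimate of the effect on all 837 eligible premises.

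**The concern.** If a customer turned away from an audited premises starts a fight somewhere else, the audited premises records one event fewer although no violence has been prevented. If the fight happens at a control premises, the contrast moves twice: down in one arm and up in the other. If it happens at an unrandomised premises, an excluded venue or a street away from any trial premises, it moves once.

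For the primary aim, which is violence recorded at licensed premises, this is a matter of interpretation. It is more serious for the ICER. A societal analysis needs violence that did not occur, whereas the model supplies violence that did not occur at that address.

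None of the related items listed above would show the difference. Contamination, understood as controls receiving the intervention, dilutes the effect, whereas displacement inflates it. The volume analysis stops at study premises. The 837-premises analysis estimates the same effect again and adds premises that may themselves receive displaced incidents. The Discussion looks ahead to use elsewhere in the UK and beyond, where authorities would need to know whether violence fell or moved.

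**Working it through.** **Inputs from the article**
- Table 1: 2,236 incidents at 837 eligible premises in 12 months; 300 audits. The 22 LA rows add up to both totals.
- Main analysis: 600 randomised, so 600 − 300 = 300 controls and 837 − 600 = 237 spare premises.
- Sample size: a 10% reduction in the failure rate is the target, read here as a ratio of 0.90.

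The stated group size of 272 can be neither reproduced nor refuted, because the exploratory trial's failure rate is not given. Nothing below depends on it.

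**Baseline volume.** 2,236 / 837 = 2.67 incidents per premises-year; × 300 = 801 per arm-year. These are incidents. The ICER unit is a session with one or more events, so 801 is an upper bound on sessions.

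**Assumed quantities** (the documents give neither)
- d = share of intervention-arm events that moves out of that arm
- s = share of those moved events that lands on controls

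**With no net prevention**

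Ratio = (1 − d) / (1 + d·s). Apparent events averted = d·(1 + s)·801. The true net change is 0.

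- 5% moved, all to controls: 0.95 / 1.05 = 0.905. About 0.05 × 801 = 40 incidents moved, seen as a gap of 80 between arms.
- 10% moved, all outside both arms: 0.90 / 1.00 = 0.90. About 0.10 × 801 = 80 incidents moved, seen as a gap of 80.

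The share needed to give exactly 0.90 is d = 0.10 / (1 + 0.90·s):

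| Destination | s | d for ratio 0.90 | Ratio at d = 10% | Apparent incidents averted at d = 10% |
|---|---|---|---|---|
| Outside both arms | 0 | 10.0% | 0.90 | 80 |
| Pro rata over the other 537 eligible premises | 300/537 = 0.559 | 6.7% | 0.85 | 125 |
| All to controls | 1 | 5.3% | 0.82 | 160 |

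**With some real prevention.** Let p be the share truly prevented: ratio = (1 − p − d) / (1 + d·s). With p = 5%, d = 5% and s = 0.559, the ratio is 0.90 / 1.028 = 0.88. Apparent over true events averted is (0.05 + 0.05 + 0.028) / 0.05 = 2.6.

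Rearranged, p = 1 − d − ratio·(1 + d·s). For an observed ratio of 0.90 and d = 5%, p is 5.0% (s = 0), 2.5% (s = 0.559) or 0.5% (s = 1).

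**The opposite direction.** If controls also improve by a share b, the ratio is (1 − p) / (1 − b). With p = 10% and an assumed b = 2%, it is 0.90 / 0.98 = 0.918, and the true benefit is understated.

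**The case against.** The case on the other side is substantial, and much of it stands.

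- **The hazard ratio answers the declared question.** The trial aim is police-recorded violence in licensed premises, and the outcome section names premises-level risk as the main interest. This stands: the primary analysis needs a label, not a replacement.
- **Proximity is inferred.** The Background sentence is general, and no distances between trial premises are given. Nine LAs with 1.1 people per hectare or fewer hold 94 of the 300 audits and 864 of the 2,236 incidents (39%). LA averages do not settle how close premises are, but it cannot be said that the arms generally share streets and customers.
- **Most audited areas would not obviously turn customers away.** Lighting, surveillance, noise, training and glassware are examples. Capacity is one example among several, and closure is reserved for clear danger. Violence that stays just outside an audited premises, or moves to another audited one, is still counted in the intervention arm.
- **Benefit can spread too**, for example through regional managers who may be responsible for several sites.
- **A statistical analysis plan may exist, and sensitivity analyses are already promised.** True, but the article itself fixes the societal perspective and the link from the model to sessions averted.

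A reader might infer that control rates are in fact raised and the hazard ratio does overstate benefit. The documents do not support this: they give no displaced share and no distances, and the two kinds of spillover act in opposite directions. A reader might also take 40 or 80 as the ICER's error. Those are incidents under an assumed share with nothing prevented, not sessions and not an estimate.

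**Conclusion.** The point holds as a limit on interpretation, and as a gap between the societal ICER and the model that feeds it. The hazard ratio remains a valid contrast between premises under this allocation, but it cannot be read as net violence prevented. The ICER does read it that way, so it can overstate net benefit.

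The size is unknown. Because the target is only a 10% reduction, an assumed displaced share of 5.3% to 10.0%, depending on destination, would reproduce it with no net prevention. This rests on assumed d and s, on Table 1 incidents standing in for sessions, and on no offsetting spread of benefit.

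How closure is handled also matters. The Sample size section accepts licence suspensions as outcomes, while the outcome section treats temporary closure as censoring. If closed time is censored, the closed premises' own lost events earn no credit, but events moved to controls still lower the ratio. The two passages must be reconciled.

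**What to change.** 1. State that the hazard ratio is a premises-level effect and not an estimate of net violence prevented.
2. Pre-specify a secondary, two-sided spillover analysis on police data already held. Model events at control premises on the number of neighbours within a fixed radius originally allocated to intervention, adjusting for total randomised neighbours and the strata, so that the contrast comes from the randomisation. Spare premises can be added, but those used as replacements must be flagged or excluded, because they may have been audited.
3. Where locations allow, describe violence at excluded venues and in nearby streets, which this model would miss. Area totals can only be descriptive, because every LA contains both arms.
4. Keep the planned ICER as the base case. Add a named scenario that varies the displaced share and its destination over a stated range, in sessions, informed by the spillover estimate.

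**Cost.** Address mapping for the 837 premises, one extra model and some added text; no new data collection and no change to the randomisation. The net estimate will be imprecise. Even for the main effect, 600 × 2.67 × 0.95 = 1,523 events give about 54% two-sided power at a ratio of 0.90 by the Schoenfeld formula, and a net estimate will be weaker. It may also be less favourable. It should support the primary analysis, not replace it.

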**Discussion:**

The results of the trial will be applicable to all statutory authorities directly involved with managing violence in the night time economy and will provide the first formal test of Health and Safety policy in this environment. If successful, opportunities for replication and generalisation will be considered.

**Trial registration:**

UKCRN 14077; ISRCTN78924818.

## Background

Alcohol related violence continues to place a considerable burden on health services [1]. Approximately 70% of unscheduled Accident and Emergency (A&E) attendances are alcohol related at peak times [2], with the bulk stemming from activities in the night time economy (NTE) [3,4]. Urban centres characterised by a high density of premises licensed for the on-site sale and consumption of alcohol typically produce a substantial share of all alcohol-related harm and are associated with severe intoxication and violent injury [5,6]. There is a growing literature detailing environment-specific risk factors in the on-licensed trade [4,7] and recognition that interventions that address these are urgently required [8,9]. However, the number of front-line police staff available to manage this environment is decreasing [10] and in the UK there is growing reliance on unevaluated industry-sponsored schemes. There is therefore a need for robust, formally evaluated interventions that can be routinely adopted by partners involved with managing the NTE. Previous evaluations of premises level (PL) interventions have a number of methodological limitations and none have been conducted in the UK.

There have been two systematic reviews in this area [4,11]. The earlier review focussed on server training interventions and concluded that research in the context of the NTE should be broadened to develop interventions that address more complex causal pathways and multiple risk factors across the full socio-ecological environment [11]. A more recent review, [4] assessed broader approaches to prevention that included responsible beverage service (RBS) training (n = 6), enhanced licensing regulation enforcement (n = 2), multi-level interventions (n = 6), licensee accords (n = 2) and a risk-focused consultation (n = 1). Only five randomised controlled trials (RCT) were identified and these were subject to a number of shortcomings including (i) considerable variation in and poorly defined outcome measures meaning studies could not be compared, (ii) follow-up periods were decided ad hoc and did not consider intervention sustainability, (iii) economic evaluations were not included, (iv) studies often relied on inappropriate control groups, (v) many failed to achieve random allocation, and (vi) participants or evaluators were not blind to study conditions. The review concluded that, while interventions that address multiple risk factors and that are designed and implemented by multi-agency and community partnerships have the potential to be effective, there is little rigorous evidence of effectiveness. It therefore recommended further development and piloting phases for complex interventions addressing multiple risk factors as a pre-requisite for their rigorous evaluation and any subsequent implementation.

The current intervention builds on earlier work that identified causative factors for violence that might be realistically targeted by interventions that are both theoretically and practically robust [12,13]. A subsequent project designed specifically to examine the case for a RCT of a multi-risk PL intervention [14] was completed. The project developed and implemented appropriate intervention content, tested its feasibility and acceptability, identified causal pathways linking intervention to violence reduction and established the feasibility of key aspects of RCT design including outcome measures, recruitment and retention. Outputs from this project were the first to rigorously test all aspects of a multi-level PL intervention in a UK context. Key findings were: (i) an enhanced multiple risk audit approach can successfully identity appropriate targets and approaches to prevention; (ii) the engagement of licensed premises and the efficacy of the intervention were maximised when implemented by statutory authorities [14]; and (iii) police recorded data on violent incidents were a valid measure of harm and sensitive to change at the PL [15]. In addition, the nested process evaluation (PE) indicated that it was necessary to engage staff across the premises hierarchy, from servers through premises managers and, where appropriate, regional managers [16] to ensure intervention receptivity.

The theoretical basis of the intervention (SMILE: Safety Management In Licensed Environments) evaluated in the current trial is that reducing known risk factors [17] within premises and their immediate environment will either directly or indirectly reduce alcohol misuse and violence and that current legislation (2003 Licensing Act, Health and Safety at Work Act 1974) provides a framework for the delivery of a risk audit intervention. Taken together, this motivates an intervention process whereby at-risk premises are first identified using police recorded violence data. Information is then shared with Environmental Health Officers (EHO) who audit and identify premises-specific risks. The intervention itself was initially developed from formative developmental studies and was further refined in an additional development phase (see Figure 1). The aim of this additional development stage was to situate the theoretical and empirical motivations for the intervention within EHO statutory authority. EHOs are not able to enforce the UK 2003 Licensing Act which is primarily focused on the sale and consumption of alcohol; however they do have available legislation that covers the operation of businesses with a view to harm reduction, including violence in the workplace. For example, businesses with five or more employees are required to undertake a formal risk assessment that should be written and available to staff. We therefore sought to identify what risks within premises might reasonably be enforced by EHOs under the Health and Safety at Work Act and developed intervention materials and guidance to EHOs to facilitate their work in these areas.

